# STUDY OBJECTIVES AND PURPOSE

## 2.1 Clinical Trial Design

This study is a Prospective, Single - center, Double-arm, Randomized-controlled Open label, safety study.

## Primary Objective

The primary objective of this study is to evaluate the safety of using the AnapnoGuard 100 system during the course of mechanical ventilation and intubation in Intensive Care Unit (ICU).

## Secondary Objective

- Evaluate the occurrence of mechanical complication due to ETT cuff over inflation.
- Physician satisfaction from AnapnoGuard system.

# 3. ENDPOINT PARAMETERS

## 3.1 Primary Endpoint Parameter

This study has primary endpoint - *rate of device related AE and SAE as a result of using AnapnoGuard 100 during mechanical intubation.* Thus, a subject's responsiveness is evaluated as following:

- A subject is considered a “success “on *safety* if no device related AE or SAE has occurred during intubation.

Serious adverse event are defined as adverse requiring operation and/or associated with prolongation of hospital stay. Serious adverse events occurrence will be compared to serious adverse events incidence in the control group of mechanically ventilated patients in intensive care units.

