**Time Table**

|  | **Screening** | **Connection to AnapnoGuard System** | **Mechanically Ventilation**  **Period** | **After AnapnoGuard Disconnection** | **Post Clearance Follow-up Phone Information** |
| --- | --- | --- | --- | --- | --- |
| **Time line** | **During hospitalization in ICU** | **Up to 6 h from intubation initiation** | **Daily evaluation** | **48h post extubation** | **1 month following extubation** |
| **Informed consent** | x |  |  |  |  |
| **Inclusion criteria** | x |  |  |  |  |
| **Medical history** | x |  |  |  |  |
| **Chest x-ray** | x | X | x* | x |  |
| **Blood tests** | x | X | x | x |  |
| **Vital signs** | x | X | x | x |  |
| **Trap bottle secretions***** |  |  | x |  |  |
| **Oxygen saturation** | x | x | x | x |  |
| **Mechanical complication assessment**** |  |  |  | x |  |
| **Subject’s general condition** |  |  | x | x | x |
| **AE and SAE** |  | x | x | x |  |
| **Study deviation** |  | x | x | x |  |
| **Final statistical analysis** |  |  |  | x |  |
| **Study exit** |  |  |  | x |  |

* Chest X-ray will be done at baseline, 48 hours after intubation and whenever there is clinical suspicion for VAP

** Mechanical complications assessment will include: spirometry, fiber optic in selected ICUs and questionnaire regarding throat pain and hoarseness.

***Recording level of trap bottle secretions 3 times a day (per shift). Records – Images and or electronic record

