This study was designed in order to evaluate the safety of the AnapnoGuard system in ICU patients ventilated for more than 12 hours. The possible complications this study aims to address are related to inappropriate cuff pressure in patients under prolonged ventilation. The complications may include mechanical complications as a result of over inflation of the cuff and leakage as a result of under inflation of the cuff. These measures are best identified and analyzed if a patient is intubated for more than 12 hours.

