## 3.2 Secondary Endpoint Parameters

- Mechanical complication occurrence due to ETT cuff over inflation will be evaluated by the following measures during the 48h post extubation:
  - Throat pain level, associated with the mechanical ventilation. Pain level will be assessed by VAS (visual analogue scale) questionnaire;
  - Hoarseness occurrence
  - Spirometry analysis
  - Fiber optic analysis (this measure will be used in selected ICUs)
- Medical staff satisfaction from AnapnoGuard 100 system operations and performance will be established by designated questionnaire for physicians and nurses.

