### 6.8 AnapnoGuard 100 System Disconnection

Prior to disconnection, during weaning from mechanical ventilation, the following will be evaluated:

- Level of sedation according to the Richmond Agitation Sedation Scale (RASS).
- Duration of the weaning process and medications usage and dosages.

After extubation, all patients will be scanned by chest x-ray.

During 48 hours following extubation, the following parameters will be used for evaluation of possible mechanical complications:

- - Throat pain level, associated with the mechanical ventilation. Pain level will be assessed by VAS (visual analogue scale) questionnaire.
  - Hoarseness occurrence
  - Spirometry analysis
  - Fiber optic analysis (this measure will be used in selected ICUs)
  - VAP Occurrence

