## To account for an approximate 15% dropout rate, we set a total number of patients N=60 (for study and control groups together).

## 8.3 Statistical Analysis

Safety of the AnapnoGuard 100 system will be evaluated by rate of AE or SAE during intubation in ICU. It is assumed that no AE or SAE will be detected wile using AnapnoGuard 100 during intubation in ICU in at least 80% of study patients.

Study hypothesis is stated in terms of Overall Proportion of Success (no AE or SAE), which is computed by total number of successes on the parameter divided by the total number in its respective cohort.

The following hypothesis is specified and will be tested:

The safety proportion of success (No AE or SAE while using AnapnoGuard 100 during intubation -R):

H0: R < 0.80

H1: R > 0.80

This hypothesis will be tested by:

1. Constructing a one-sided, lower 95% confidence interval about the observed Overall Proportion of Success in the relevant cohort
2. Examining whether the lower limit of the confidence interval is at or above the success criterion

Study success will be declared if the following is met:

1. Lower confidence limit of *rate of AE and SAE as a result of using AnapnoGuard 100 during mechanical intubation* success is at 0.80 or above.

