## 9.3 Guidelines to Determine the Relationship of an AE/SAE to the Study Device/Procedure

- Definite: The adverse event is clearly related to the investigational treatment.
- Probable: The adverse event is likely related to the investigational treatment.
- Possible: The adverse event may be related to the investigational treatment.
- Unlikely: The adverse event is doubtfully related to the investigation treatment.
- Unrelated: The adverse event is clearly NOT related to the investigational agent(s).

Potential Adverse Events that may occur during the study in both the study (AnapnoGuard) and control groups are related to hyper/hypo inflation of the ETT cuff and suction dysfunction. The Adverse Events are listed in the table below:

| **Potential Adverse Events** | | **Severity** |
| --- | --- | --- |
| Over inflation of the cuff resulting in: | Hoarseness / Throat pain | Mild |
| Tracheal Stenosis | Moderate - Severe |
| Tracheal rupture | Severe |
| Under inflation of the cuff resulting in: | Leakage detected by ventilator | Mild |
| Decrease in saturation | Mild - Moderate |
| Apnea | Severe |
| Suction Dysfunction resulting in: | Tracheal Edema | Mild |
| Mucosal Injury | Mild - Moderate |
| Tracheal Ulcerations | Moderate |

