## 9.7 Clinical Management of Study Related Adverse Events

AEs will be clinically managed according to medical indications, Local Health Authority, GCP and the standard of care in the specific Medical Center. Subjects will be entitled for continuation of clinical follow-up and treatment until of their study related clinical problem has been resolved, even beyond the pre-defined 1 month follow-up period.

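### The success rule counts device-related events during intubation, but the planned checks for cuff over-inflation injury come only in the 48 hours after extubation

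*Protocol*

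**What the plan says.** - **Success rule.** Under section 3.1 and the synopsis, a patient is a success "if no device related AE or SAE has occurred during intubation". Section 8.3 carries the same window into the analysis: "Safety of the AnapnoGuard 100 system will be evaluated by rate of AE or SAE during intubation in ICU". Study success follows if the one-sided lower 95% limit for the success proportion is at least 0.80.
- **Harms of interest.** The last paragraph of the Clinical background says the study addresses complications of inappropriate cuff pressure: "The complications may include mechanical complications as a result of over inflation of the cuff", and leakage from under-inflation. Section 9.3 lists "Hoarseness / Throat pain", tracheal stenosis and tracheal rupture as potential adverse events of over-inflation.
- **When they are assessed.** Section 3.2: "Mechanical complication occurrence due to ETT cuff over inflation will be evaluated by the following measures during the 48h post extubation". Section 6.8: "During 48 hours following extubation, the following parameters will be used for evaluation of possible mechanical complications". The Time Table marks this assessment only in the column 48 hours after extubation, and its footnote gives the content: "Mechanical complications assessment will include: spirometry, fiber optic in selected ICUs and questionnaire regarding throat pain and hoarseness".
- **Adverse event collection.** The Time Table collects AE and SAE up to 48 hours after extubation. That row is blank at the 1-month call, and study exit and the final statistical analysis are both placed at 48 hours. Section 9.7, however, speaks of care continuing "even beyond the pre-defined 1 month follow-up period".
- **Tabulation.** Section 8.1 tabulates adverse events by arm, severity and relation to treatment, with no limit to the intubation period.

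**The concern.** The window that decides the trial closes at extubation. The examinations planned to find over-inflation injury start after that. A patient whose first sign of related airway injury appears at the 48-hour assessment would have a recorded, device-related adverse event and would still be a success under section 3.1.

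The trial could therefore meet its safety criterion while injuries of the kind it set out to study stay outside the criterion. Section 3.1 also leaves room for doubt. Its endpoint title attributes events to use of the device, whereas its operative definition speaks of when they occurred. Two analysts could classify the same late-detected injury differently.

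A related gap lies further out. An injury that becomes apparent between 48 hours and 1 month has no adverse event entry planned at the one contact where it could be asked about.

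**Working it through.** **1. The passages side by side**

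| Element | Where | Timing |
|---|---|---|
| Success or failure of a patient | 3.1, 8.3, synopsis | during intubation |
| Throat pain, hoarseness, spirometry, fibre-optic examination | 3.2, 6.8, Time Table | 48 h after extubation |
| AE/SAE recording | Time Table | connection to 48 h after extubation |
| AE tables by arm and relation | 8.1 | no window stated |
| 1-month call | Time Table | general condition only; AE/SAE row blank |

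An injury first found at 48 hours is in rows 2 to 4 and, on the plain reading of 3.1, not in row 1.

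**2. How many failures the rule tolerates**

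Inputs: success threshold 0.80 and one-sided 95% lower limit (8.3); 25 evaluable patients per arm, 60 in total (8.2 and the sentence following it). The allowance reproduces: 50/(1 − 0.15) = 58.8, so 59, rounded up to 60, or 30 per arm. The power claimed for N=25 is not used here.

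The protocol names no interval method. Formulas for x successes in n, with p = x/n and z = 1.645:
- Clopper-Pearson: the 0.05 quantile of Beta(x, n − x + 1)
- Wald: p − z√(p(1 − p)/n)
- Wilson: [p + z²/(2n) − z√(p(1 − p)/n + z²/(4n²))] / (1 + z²/n)

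| Result | Clopper-Pearson | Wilson | Wald |
|---|---|---|---|
| 24/25 | 0.824 pass | 0.839 pass | 0.896 pass |
| 23/25 | 0.769 fail | 0.785 fail | 0.831 pass |
| 22/25 | 0.718 fail | 0.735 fail | 0.773 fail |

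So 25 patients allow one failure by Clopper-Pearson or Wilson, and two by Wald.

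**3. An example with 30 device patients**

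Assume no related event during intubation and three related injuries first found within 48 hours of extubation. Both counts are assumed.
- Events during intubation only: 30/30, Clopper-Pearson limit 0.05^(1/30) = 0.905, pass.
- Events through 48 hours: 27/30. Clopper-Pearson gives 0.761 and Wilson 0.77, both fail. Wald gives 0.90 − 1.645 × √(0.9 × 0.1/30) = 0.90 − 1.645 × 0.0548 = 0.810, pass.
- With one more event, 26/30, Wald gives 0.765, fail.

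**4. A range of assumed harm rates**

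Assume a true success rate of 0.97 during intubation and an independent proportion h of patients with a countable event first found after extubation, so that p = 0.97(1 − h). The documents give neither figure. The chance of passing with n = 25 is P(X ≥ 24) for Clopper-Pearson or Wilson and P(X ≥ 23) for Wald, with X binomial(25, p).

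| h | p | At least 24/25 | At least 23/25 |
|---|---|---|---|
| 0 | 0.970 | 83% | 96% |
| 5% | 0.921 | 41% | 69% |
| 10% | 0.873 | 16% | 37% |
| 20% | 0.776 | 1.5% | 6% |

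**The case against.** The strongest reply is that the endpoint matches its objective. Section 2 defines the primary objective as safety during ventilation and intubation, and makes over-inflation complications a separate secondary objective with its own 48-hour measures. On that reading, the placement is a declared hierarchy. This stands in part: one cannot say that the primary endpoint fails its stated primary objective. It does not remove the tension with the Clinical background, nor the fact that study success is declared on the primary rule alone.

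A reader might also infer more than the documents support:
- *That over-inflation harm cannot count at all.* It can, if it shows while the tube is in place; tracheal rupture is an example. An injury inflicted during intubation but seen later might also be argued to count, given the endpoint title.
- *That late injury would appear only in secondary tables.* Section 8.1 tabulates adverse events by arm and relation without a window.
- *That ulceration and mucosal injury are among the over-inflation harms left out.* Section 9.3 lists them under suction dysfunction, and the whole list applies to both arms.
- *That later stenosis would necessarily be missed.* Section 9.4 requires adverse events during the study to be recorded and followed to resolution, and the 1-month call asks about general condition. What is absent is a planned adverse event question at that call.
- *That 27/30 is a failure.* By Wald it passes, and section 8.2 uses a normal approximation for its power calculation.

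Finally, section 8.2 justifies 0.80 by earlier patients without related events during intubation. A wider window goes beyond that basis. This is correct, and the amended text should say so.

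**Conclusion.** The point holds in a limited form. The success rule is confined in time to intubation, and the planned assessments for over-inflation complications fall wholly after it. Related injury first found at 48 hours would be visible in the adverse event tables but, on the plain reading, absent from the rule that declares success. Section 3.1 leaves enough ambiguity that the matter should be settled before data are seen.

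The size cannot be estimated from the protocol, because no post-extubation harm rate is given. With room for only one or two failures in 25, a few such events could decide the result. How many depends on the interval method, which the protocol does not name. The example counts and the rates in the range above are assumptions.

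The blank adverse event cell at 1 month, with study exit and final analysis at 48 hours, is a smaller inconsistency with section 9.7.

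**What to change.** 1. In sections 3.1, 8.2 and 8.3 and in the synopsis, define failure as a device-related AE or SAE with onset or detection from the start of intubation through the scheduled 48-hour post-extubation assessment.
2. Keep hoarseness and throat pain, which section 9.3 grades as mild, as the existing secondary measure, so that the 0.80 criterion is not driven by them.
3. State in section 8.2 that the pilot basis for 0.80 covered events during intubation.
4. Mark the AE/SAE row at the existing 1-month call in both arms. Reconcile the 48-hour placement of study exit and final analysis with the 1-month period in section 9.7.

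Cost: wording and a few questions at a call already planned, with no new visit. The success proportion may be less favourable, and the final analysis waits for the 1-month call. Since fibre-optic examination is limited to selected ICUs, the text should also say how a patient without a complete 48-hour assessment is classified.

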## 9.2 Definition of Serious Adverse Event (SAE)

Any adverse event experience that results in any of the following outcomes:

- Death
- A life threatening event
- Requires or prolongs inpatient hospitalization or re hospitalization
- Persistent or significant disability/incapacity
- Medical or surgical intervention to avoid impairment of body function

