## 9.6 List of Serious Adverse Events

Serious, procedure related adverse events include those events with one or more of the following outcomes:

- Death: The subject’s death is suspected as being a direct outcome of the adverse event.
- Life-Threatening: The subject was at eminent risk of dying at the time of the adverse event or it is suspected that the use of the device or continuation of the procedure would have resulted in the subject’s death.
- Hospitalization (initial or prolonged):The use of the device or procedure was associated with an adverse event that resulted in the subject’s readmission to the hospital (>24 hours) or the prolongation of a hospital stay by >24 hours beyond the standard of care in the specific site.
- Disability: The use of the device or procedure was associated with an adverse event that resulted in significant, persistent, or permanent change, impairment, damage, or disruption in a subject’s body function/structure, physical activities, or quality of life.
- Requires Intervention to Prevent Permanent Impairment or Damage of a Body Part and/or Function: The use of the device or procedure resulted in a condition that required medical or surgical intervention to preclude permanent impairment or damage to a subject.

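### Section 3.1 defines an SAE more narrowly than section 9.2, so the promised SAE comparison with control could omit fatal or life-threatening events that are reported as SAEs

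*Protocol*

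**What the plan says.** Protocol section 3.1 (Primary Endpoint Parameter) states: "Serious adverse event are defined as adverse requiring operation and/or associated with prolongation of hospital stay". It does not refer to section 9. The sentence that follows puts the term to use: "Serious adverse events occurrence will be compared to serious adverse events incidence in the control group of mechanically ventilated patients".

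Section 9.2 is the protocol's formal SAE definition. It opens with "Any adverse event experience that results in any of the following outcomes" and lists five: death; "A life threatening event"; "Requires or prolongs inpatient hospitalization or re hospitalization"; "Persistent or significant disability/incapacity"; and "Medical or surgical intervention to avoid impairment of body function".

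Section 9.4 requires SAEs to be reported to the sponsor's representative and recorded on the CRF and SAE form, using the definitions given before it.

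Section 9.6 adds a list introduced by "Serious, procedure related adverse events include those events with one or more of the following outcomes". It has the same five outcome classes as 9.2, but counts readmission or a prolonged stay only when it exceeds 24 hours.

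**The concern.** The protocol fixes one term in two incompatible ways and attaches the narrower one to a comparison between the arms. The trial's sole primary objective is safety, so a reader will expect deaths and life-threatening events to be at the centre of any SAE comparison. Under 3.1 as worded, such an event enters only if it also led to an operation or a longer stay.

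Two consequences follow. The comparison with control could miss the gravest events. The SAE count in that comparison would also differ from the count reported under section 9, with no rule saying which governs. The trial is open label (section 2.1), so a choice between definitions made after events are known would be open to challenge.

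**Working it through.** No sample size, power or event figure bears on this point, so there is nothing to recompute. The check is a comparison of the criteria.

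**Step 1: coverage of the 9.2 outcomes by 3.1**

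| Outcome class in 9.2 | Covered by 3.1? |
| --- | --- |
| Death | No |
| Life-threatening event | No |
| Hospitalization required or prolonged, or rehospitalization | In part: prolonged stay only |
| Disability or incapacity | No |
| Medical or surgical intervention to avoid impairment | In part: operation only |

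Three of the five classes are absent and two are partly covered. Rehospitalization and non-operative medical intervention fall in the uncovered parts.

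**Step 2: which definition each activity uses.** Section 9.4 comes after 9.2 and before 9.6, so its backward reference is most naturally to 9.2. The comparison with control stands directly after the 3.1 definition, so its natural reading is the narrow one. Reporting and comparison therefore rest on different definitions.

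**Step 3: an example from the protocol's own list.** Section 9.3 names apnea from cuff under-inflation as a potential event in both groups, graded severe. Severity is not seriousness, so suppose an episode that is life-threatening but resolves without an operation and without a longer stay. It is an SAE under 9.2 and not under 3.1. A fatal event with neither an operation nor a longer stay is classified in the same way.

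**Step 4: effect on the primary endpoint.** A subject fails if a device-related AE or a device-related SAE occurs during intubation (synopsis and 3.1). Under either definition an SAE is an adverse event with additional features, so SAEs are a subset of AEs. The union of AEs and SAEs is then the set of AEs, and moving the seriousness boundary changes no subject's status. Section 8.3 in places omits the restriction to device-related events, but it uses the same AE-or-SAE composite, so the argument holds there too.

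**Step 5: section 9.6 against 9.2.** The five outcome classes match. The concrete difference is the threshold: a procedure-related event that prolongs the stay by less than 24 hours meets 9.2 (and 3.1) but not the hospitalization item in 9.6.

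**The case against.** The best defence is that little is lost. Section 9.4 sends all 9.2 SAEs to the CRF and SAE form, so no event goes uncollected. The hypothesis in 8.3 concerns the AnapnoGuard success proportion alone, and the SAE comparison in 3.1 has no hypothesis or test attached. Section 8.1 promises AE tables by arm, with severity and relatedness, so a fatal event would appear there whatever it is called. All of this stands and limits the point. It does not settle which definition the comparison in 3.1 uses.

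Several stronger readings are tempting, and the documents do not support them:

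- *The primary endpoint is compromised.* It is not, because any device-related AE is already a failure.
- *This is the protocol's only safety comparison between arms.* The AE tables by arm in 8.1 contradict that.
- *The narrow rule favours the arm with more deaths.* Death can cut a stay short, but it can also follow an operation or a prolonged stay. The protocol gives no mortality or length-of-stay data, so a direction of bias cannot be asserted.
- *The number of omitted deaths can be estimated from ICU mortality.* The protocol gives no mortality figure. Some deaths would meet 3.1 through an operation or a longer stay, and not every ICU death need be the outcome of an adverse event. No count is defensible.
- *Section 9.6 is a rival definition that drops serious outcomes.* It carries the same five classes for procedure-related events. Only its 24-hour threshold needs reconciling.

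**Conclusion.** The contradiction is real and stands in current text. Section 3.1 omits three of the five outcome classes in 9.2 and narrows the other two, and it attaches that narrower definition to the comparison with control. Read literally, that comparison could exclude fatal or life-threatening events and would disagree with SAE reporting.

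The consequence is confined to the SAE comparison and its counts. The primary endpoint, the 8.3 test, event collection and the AE tables in 8.1 are untouched. The conclusion assumes that 3.1 is read as a closed definition, which is how it is worded, and that the comparison uses the definition immediately before it. It is an internal inconsistency that should be corrected, with no numerical size attached.

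**What to change.** - In 3.1, replace the SAE sentence with a cross-reference: 'SAE as defined in 9.2'.
- In the next sentence of 3.1, state that the comparison with control uses all 9.2 SAEs in both arms, with device-related SAEs shown as a subset.
- In 9.6, state that the list elaborates 9.2 for procedure-related events and that relatedness is a separate judgement. Reconcile its 24-hour threshold with 9.2, so that one rule on prolonged stay and readmission applies throughout.

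The cost is a few sentences in 3.1 and 9.6. Because 9.4 already has SAEs under the section 9 definition recorded on the CRF and SAE form, no new data or procedures are needed and the sample size is unaffected.
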